## Abstract

**Background:**

Postoperative gastrointestinal (GI) dysfunction (PGD) is a common problem after abdominal surgery. PGD can increase the length of hospital stay and may lead to serious complications. Acupuncture and moxibustion are alternative therapies for PGD that have been used in some settings. However, the effect of preventive application of acupuncture or transcutaneous electrical acupuncture stimulation (TEAS) is still uncertain. The purpose of this study is to investigate the efficacy of the continuous application of TEAS on GI function recovery in adults undergoing abdominal surgery. At the same time, we will try to confirm the mechanism of TEAS through the brain–gut axis.

**Methods/design:**

This study is a prospective, single-center, two-arm, randomized controlled trial that will be performed in a general hospital. In total, 280 patients undergoing abdominal surgery were stratified by type of surgery (i.e. gastric or colorectal procedure) and randomized into two treatment groups. The experimental group will receive TEAS stimulation at L14 and PC6, ST36 and ST37. The sham group will receive pseudo-TEAS at sham acupoints. The primary outcome will be the time to the first bowel motion by auscultation. The recovery time of flatus, defecation, the changes in perioperative brain–intestinal peptides, postoperative pain, perioperative complications, and hospitalization duration will be the secondary outcomes.

**Discussion:**

The results of this study will demonstrate that continuous preventive application of TEAS can improve the GI function recovery in patients undergoing abdominal surgery and that this effect may act through brain–gut peptides.

**Trial registration:**

Chinese Clinical Trial Registry, ChiCTR1900023263. Registered on 11 May 2019.

## Introduction

Postoperative gastrointestinal dysfunction (PGD) refers to a series of clinical syndromes in which digestive tract symptoms are the main manifestation after a surgical operation. The most common postoperative syndromes affect the gastric, intestinal, and biliary tract systems, and patients often experience symptoms such as abdominal distension, constipation, nausea and vomiting, and defecation disorders. The incidence of PGD can be as high as 10%–30% [1, 2]. Despite ongoing research and different new drug treatments, the incidence of abdominal distention within 24 h of an operation is 8%–28% of all surgeries [3]. Patients with PGD have a longer duration of hospitalization, heavier economic burdens, and a much higher risk of serious complications, such as infection, electrolyte disturbances, and even life-threatening conditions [3–5]. Therefore, for postoperative patients in the hospital, restoring the normal function of the gastrointestinal (GI) tract as soon as possible for postoperative rehabilitation is a very important step.

Once PGD appears, the main treatment measures that can be taken include the use of gastric dynamics promoting drug, GI decompression, nutritional support, non-steroidal anti-inflammatory drug treatments, and so on [2, 6]. However, the therapeutic effect of these treatments is limited, and the patients’ satisfaction rate is relatively low [6]. Currently, many studies have demonstrated that acupuncture and moxibustion have unique advantages in the treatment of PGD [7] and have gradually obtained more acceptance from physicians as an alternative therapy.

Recently, the brain–gut axis, serving as a bridge between the central nervous system (CNS) and the GI tract [8, 9], has been proved to be one of the possible mechanisms of acupuncture improving GI. Through the brain–gut axis, signals from the brain affect the sensory, motor, and endocrine modalities, as well as the microflora of the GI gut. Similarly, visceral information from the microbiota may also influence brain functions [8]. In our previous studies, our research group also found that electroacupuncture stimulation of Zusanli (ST36) could lead to imaging changes in different brain regions observed by functional magnetic resonance imaging (fMRI) [10]. These results demonstrated that acupuncture may act through the brain–gut axis. Brain–gut peptides are distributed along the GI tract and in the CNS and are involved in the modulation of GI tract processing [11]. The secretion of substance P (SP) and vasoactive intestinal polypeptide (VIP) are decreased, motilin and cholecystokinin (CCK) are increased after treatment with electrical acupuncture (EA) in rats with irritable bowel syndrome (IBS) [12, 13]. However, until now, most research on this mechanism has focused on animal studies and the treatment effect of acupuncture or transcutaneous electrical acupuncture stimulation (TEAS) on patients after abdominal surgery—whether the prevention effect of TEAS on PGD through brain–gut peptides or not—is still unclear.

Based on previous studies, our aim is to confirm the preventive effect of TEAS on PGD in patients undergoing abdominal surgery. Changes in the perioperative brain–gut peptides may prove that the regulation of GI function by TEAS stimulation plays a role through the brain–intestinal axis. Health economic indicators (length of stay, cost of hospitalization, etc.), will also demonstrate the significance of perioperative TEAS stimulation on postoperative GI function recovery of patients undergoing abdominal surgery. This study will provide further evidence as to whether TEAS should be included in enhanced recovery after surgery (ERAS) protocols for patients undergoing GI surgery.

## Methods

The protocol for this trial is reported based on the Standard Protocol Items: Recommendations for Interventional Trials (SPIRIT) 2013 Checklist: defining standard protocol items for clinical trials (Additional file 1). The study has been approved by the Ethics Committee of Beijing Friendship Hospital (approval number 2019-P-065-01) and has been registered in the Chinese Clinical Trial Registry (Chictr) (registration number ChiCTR1900023263). This study is still in process.

### Trial design

The trial is a single-center, prospective, randomized controlled trial (RCT) with a two-arm, parallel-group design (Fig. 1). Data analysis will be performed according to the superiority principle. The study will be carried out at Beijing Friendship Hospital and will be performed according to the principles of the Declaration of Helsinki (version Edinburgh 2000).

**Fig. 1 Fig1:**
[figure not shown]
Consolidated Standards of Reporting Trials (CONSORT) diagram for this trial

The study will continue for 24 months, and all the selected individuals will be stratified by type of surgery (i.e. gastric or colorectal procedure) and randomized into two groups: the TEAS treatment group (Group T) and the sham group (Group S). The researchers will conduct screening in accordance with the established criteria and pre-standard treatment plan. Data collection will start from the collection of basic data until the end of follow-up (Table 1).

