### Randomization and blinding

This is a single-blinded study. The doctors from the traditional Chinese department who will conduct the TEAS stimulation and the anesthesiologists will know the grouping information and participants. The observers of major outcomes after surgery will be blinded. Randomization will be conducted by a computer-generated blocked randomization list with 70 blocks of four patients per block. The participants will be consecutively randomly assigned to the TEAS group or the sham group at a ratio of 1:1. Allocation shall proceed via duplicate, sealed, numbered envelopes, which will be stored by the clinical trial quality control inspectors and the main person in charge of this research group. The blind bottom shall not be opened without reason during the trial. The outcome assessors and the statisticians will not participate in the treatment, they will perform the outcome evaluation and the statistical analysis independently.

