### Sample size calculation

Due to a lack of related reports on the preventive usage of TEAS in patients undergoing GI surgery, we evaluated the effectiveness of TEAS according to our pre-experimental results. A priority-effectiveness test was used and the ratio between the groups was 1:1. According to the pre-experimental results, a difference in time to first bowel sounds of 12 h was thought to be clinically significant and selected as the effect size. This result in a hazard ration of 1.5. The COX regression sample size calculation formula was used to complete the sample size estimation. We set unilateral α = 0.05 and power = 0.90; PASS 2011 software was used for sample estimation and a total of 256 effective cases were estimated. According to the above sample estimation result and assuming 10% patient loss, a minimum of 280 cases is required. Therefore, we have set the required number of cases in this study to 280 cases, including 140 cases in the TEAS group and 140 cases in the sham TEAS group. Our General Surgery Department performs 400–500 cases of GI surgery per year; consequently, this study period is set at 2 years.

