### Statistical methods

Statisticians are responsible for negotiating with major researchers to develop statistical analysis plans, establish databases, and conduct statistics with the SPSS statistical analysis system. All data will be collated by statisticians. The intention processing principle in SPSS 22.0 will be used for the data analysis. A unilateral test will be used for statistical results, and a *P* value < 0.05 will be considered statistically significant. The results will be expressed as the mean ± standard deviation. The t-test will be used for the normality and homogeneity of data, the hypothesis test of superiority will be used for major outcome indicators, the chi-square test will be used for normal distribution data, and the rank sum test or Fisher’s exact probability method will be used for non-normal distribution data. Statistical methods for the main efficacy indicators have been determined by the Capital Medical University statistical department.

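### Stratified randomisation by surgery type is claimed, but the list as described does not deliver it, and the tests named do not use surgery type

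*Protocol article*

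**What the plan says.** Stratification is stated twice. The abstract (Methods/design) has "280 patients undergoing abdominal surgery were stratified by type of surgery (i.e. gastric or colorectal procedure" procedures, and the Trial design section says that patients are "stratified by type of surgery (i.e. gastric or colorectal procedure) and randomized into two groups".

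Randomization and blinding is the only section that describes how the sequence is made: "Randomization will be conducted by a computer-generated blocked randomization list with 70 blocks of four patients per block". It continues: "The participants will be consecutively randomly assigned to the TEAS group or the sham group at a ratio of 1:1". Concealment is described as "Allocation shall proceed via duplicate, sealed, numbered envelopes". The section mentions no stratum, no second list and no envelope set per surgery type.

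Sample size calculation plans "280 cases, including 140 cases in the TEAS group and 140 cases in the sham TEAS group", uses a Cox formula with a hazard ratio of 1.5, and gives no stratum term. Statistical methods names the t-test ("The t-test will be used for the normality and homogeneity of data"), the chi-square test, the rank sum test and Fisher's exact test. For the main outcome it names only a superiority test, without a model. It also says that an analysis plan will be developed. That plan is not shown.

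**The concern.** Blocking balances the arms only within the list being blocked. If gastric and colorectal patients draw from the same blocks in order of arrival, each block mixes the two types. The list then balances the total but not either type. The sponsor chose surgery type as the factor worth balancing, and the primary outcome is time to return of bowel sounds, so the eventual report could claim a balance that the procedure did not secure.

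The analysis follows from this. If allocation was stratified, a test that ignores the stratum does not use the design. If it was not, adjustment is the remaining protection against a chance imbalance. The tests named do neither.

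**Working it through.** **1. List length.** 70 blocks × 4 = 280, which equals the planned total (140 + 140). The figure reproduces, and it leaves no spare blocks.

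**2. Could 70 blocks serve two strata?** The blocks needed are ceil(n1/4) + ceil(n2/4), with n1 + n2 = 280. A split of 120/160 needs 30 + 40 = 70. A split of 110/170 needs 28 + 43 = 71. Seventy suffice only if both counts are multiples of four. To divide them beforehand, the split must also be known in advance. Study participants and recruitment sets no quota by surgery type.

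**3. Balance under one common list.** Let d be the TEAS-minus-sham difference within one surgery type that makes up a share p of patients. Because the arms are equal overall, Var(d) = 280 × p(1 − p). The article gives no share, so p is assumed. The probabilities and percentiles come from 40,000 simulated lists.

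| p | SD by formula | SD simulated | difference ≥ 10 | 95th percentile |
|---|---|---|---|---|
| 20% | √44.8 = 6.7 | 6.7 | 15% | 13 |
| 30% | √58.8 = 7.7 | 7.7 | 22% | 15 |
| 50% | √70 = 8.4 | 8.4 | 25% | 16 |

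A difference of 13 to 16 is 9 to 11 percentage points between arms of 140. With separate lists in blocks of four, only the last block of each list can be incomplete, so the difference is at most 2 per stratum.

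**4. Power at the stated level.** The plan says "We set unilateral α = 0.05 and power = 0.90". The inputs are 256 events and a hazard ratio of 1.5. The reference power is Φ(√256 × ln 1.5 / 2 − 1.645) = Φ(3.244 − 1.645) = Φ(1.599) = 94.5%. This is above 90% because 256 is the requirement for a two-sided 0.05 test, which is a separate matter.

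Log-rank power (%) was simulated with 3,000 trials per row, exponential times and no censoring (Monte Carlo SE about 0.4-0.7 points):

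| Between-stratum HR | share | common list, unstratified test | common list, stratified test | separate lists, unstratified test | separate lists, stratified test |
|---|---|---|---|---|---|
| 1.0 | 30% | 94.7 | 94.4 | 94.4 | 93.9 |
| 1.0 | 50% | 94.4 | 94.2 | 94.3 | 94.0 |
| 1.5 | 30% | 93.5 | 94.1 | 93.6 | 94.2 |
| 1.5 | 50% | 93.0 | 93.4 | 92.9 | 94.1 |
| 2.0 | 30% | 91.1 | 93.7 | 92.4 | 94.6 |
| 2.0 | 50% | 90.9 | 94.7 | 91.0 | 93.5 |
| 3.0 | 30% | 88.5 | 93.8 | 90.0 | 94.0 |
| 3.0 | 50% | 85.0 | 94.1 | 87.2 | 94.1 |

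The loss is the first power column against the last. At HR 1.5 it is 0.7 and 1.1 points, at HR 2 it is 3.5 and 2.6, and at HR 3 it is 5.5 and 9.1. Further runs under the same assumptions gave 0-2, 4-5 and 9-10 points. The ranges quoted (0-2, 3-5, 5-10) cover both sets.

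**5. Validity.** With separate lists and an unstratified test, simulated type I error is 4.4-5.4% at HR up to 2, within simulation error of 5% or slightly below it. At HR 3 it is 4.6% and 3.6%. The test does not exceed its level and becomes conservative as the stratum becomes more prognostic.

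**The case against.** The strongest reply is that a journal article condenses the full protocol, and that an analysis plan exists or will exist. Parts of this stand, and they rule out several readings that a reader might infer.

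- *That the trial was in fact randomised from one unstratified list.* The singular list, consecutive assignment and exact 280 point strongly that way, but the article does not say so. Seventy blocks divided between two strata with fixed targets are not excluded. The condensed format does not remove the conflict, however, because the section that gives the specific block numbers is the one that does not fit the stratification claim.
- *That no analysis will use surgery type.* This is true of the tests printed. But the model for the primary outcome is not named, and adjustment for a randomisation factor is commonly left to the analysis plan. Silence here is not a decision, and on its own it would not be a finding.
- *That balance is unsecured and stratified precision is also lost.* These belong to alternative scenarios. With one common list there is no stratified design to waste, only a covariate adjustment not made. With separate lists the balance is secured.
- *That the power loss is necessarily serious.* The article gives no prognostic strength for surgery type. At a between-stratum ratio of 2, unstratified power is still about 91% at the stated one-sided 0.05, above the 90% target. It falls clearly below target only near a ratio of 3.

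**Conclusion.** The point holds as an inconsistency that must be reconciled, with an inexpensive improvement to the analysis attached. The abstract and Trial design claim stratification by surgery type; Randomization and blinding, as written, does not deliver it; the tests named do not use surgery type. The documents do not settle which procedure was followed.

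Under one common list, balance by surgery type is a matter of chance, with the 15-25% frequency of sizeable differences shown above. Under separate lists, the cost is a conservative test, not an invalid one. The power loss ranges from nothing detectable to about 10 points, depending on how prognostic surgery type is. All these figures rest on assumed shares (20-50% for balance, 30-50% for power) and assumed between-stratum hazard ratios of 1 to 3.

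**What to change.** Trial status reports 106 participants recruited, so the list already exists and the text has to describe what was done.

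1. State which procedure was actually used. If each surgery type had its own list and envelope set, correct Randomization and blinding to say so, with the block numbers per list. If one common list was used, withdraw the stratification claim from the abstract and Trial design.
2. In either case, prespecify before unblinding that the primary time-to-event analysis (Cox or log-rank) is stratified by, or adjusted for, surgery type. The table shows that the stratified test keeps power at about 93-95% under both allocation procedures.
3. Adjusting every secondary comparison is optional.

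The cost is a corrected description and one line of analysis wording. Surgery type is already known for every patient, so no new data are needed. When surgery type is not prognostic, any power given up by stratifying is within simulation error.

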**Table 1 Tab1:**
[figure not shown]
Standard Protocol Items: Recommendations for Interventional Trials (SPIRIT) Schedule for enrollment, interventions, and assessments

### Randomization and blinding

This is a single-blinded study. The doctors from the traditional Chinese department who will conduct the TEAS stimulation and the anesthesiologists will know the grouping information and participants. The observers of major outcomes after surgery will be blinded. Randomization will be conducted by a computer-generated blocked randomization list with 70 blocks of four patients per block. The participants will be consecutively randomly assigned to the TEAS group or the sham group at a ratio of 1:1. Allocation shall proceed via duplicate, sealed, numbered envelopes, which will be stored by the clinical trial quality control inspectors and the main person in charge of this research group. The blind bottom shall not be opened without reason during the trial. The outcome assessors and the statisticians will not participate in the treatment, they will perform the outcome evaluation and the statistical analysis independently.

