## Trial status

The first participant was enrolled on September 1, 2019, and the first version was developed on August 20, 2019. The recruitment will be completed on December 31, 2020. Shown above is the third version whose protocol was revised for the following reasons: unspecific statistical methods; imprecise sample size calculation; and inappropriate descriptions. To date, 106 participants have been recruited. This trial is still ongoing.

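### A single fixed, disclosed block size of four, with unblinded treating staff not stated to be separate from recruiting staff, puts allocation concealment at risk

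*Protocol article*

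**What the plan says.** All references are to the Protocol article.

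- **List.** Randomization and blinding: "Randomization will be conducted by a computer-generated blocked randomization list with 70 blocks of four patients per block".
- **Order and ratio.** Same section: "The participants will be consecutively randomly assigned to the TEAS group or the sham group at a ratio of 1:1".
- **Who is unblinded.** Same section: "The doctors from the traditional Chinese department who will conduct the TEAS stimulation and the anesthesiologists will know the grouping information and participants".
- **Concealment.** Same section: "Allocation shall proceed via duplicate, sealed, numbered envelopes, which will be stored by the clinical trial quality control inspectors". Custody is shared: "and the main person in charge of this research group".
- **Setting.** Trial design: "The trial is a single-center, prospective, randomized controlled trial (RCT) with a two-arm, parallel-group design". That section also stratifies by gastric or colorectal procedure. It does not say how the 70 blocks are divided between the two strata.
- **Screening.** Trial design assigns screening to the researchers and does not identify them further. Study participants and recruitment places recruitment after eligibility and signed consent.
- **Progress.** Trial status: "To date, 106 participants have been recruited. This trial is still ongoing".

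**The concern.** Sealed envelopes hide the next slip. They do not hide an arm that can be worked out from patients already allocated. In a block of two TEAS and two sham patients, the fourth allocation follows from the first three, and the third follows whenever the first two were alike. With one centre, one block size and 1:1 allocation, the only further ingredient needed is knowledge of past arms, and two groups of treating staff have that by design.

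If such knowledge reached the people who decide whether, or when, a patient is approached, consented or scheduled, patients expected to recover quickly or slowly could be steered towards one arm, even without intent. The groups would then differ at entry. Blinded auscultation protects the measurement of the primary outcome but does not correct a difference that was there before treatment.

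**Working it through.** **Inputs.** Block size 4, 70 blocks, 1:1 (Randomization and blinding); total 280 (Sample size calculation); 106 recruited (Trial status).

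**List size.** 70 × 4 = 280, which reproduces the planned total. The whole trial therefore runs on blocks of one size.

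**Predictability in a block of four.** There are 6 equally likely orderings of two TEAS and two sham. For an observer who knows all earlier allocations and the block boundaries:

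| Position | Probability that the arm is certain | Probability that the best guess is right |
|---|---|---|
| 1 | 0 | 1/2 |
| 2 | 0 | 2/3 |
| 3 | 1/3 (first two alike) | 1/3 × 1 + 2/3 × 1/2 = 2/3 |
| 4 | 1 | 1 |

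- Certain in advance: (1/3 + 1)/4 = 1/3 = 33.3%.
- Best guess right: (1/2 + 2/3 + 2/3 + 1)/4 = (17/6)/4 = 70.8%, against 50% for a sequence that cannot be predicted at all.

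**In patients.** Over the whole trial, 280 × 1/3 = 93. Remaining when the article was written: 280 − 106 = 174, and 174 × 1/3 = 58. The same fractions apply within each surgery stratum if the observer tracks the strata separately, apart from incomplete last blocks.

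**What varying the block size would achieve.** Fixed blocks were enumerated exactly. Random sizes were simulated (400 lists of 280) for an observer who knows the set of sizes and all past allocations but not the order of the sizes. The sizes are assumptions for illustration. Run on fixed blocks of 4, the simulation gave 33.4% and 70.8%, in agreement with the enumeration.

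| Scheme | Certain in advance | Best guess right |
|---|---|---|
| Fixed 4 (the plan) | 33.3% | 70.8% |
| Fixed 6, known | 25% | 68.3% |
| Fixed 8, known | 20% | 66.6% |
| Random 4 or 6 | 5.4% | 69.3% |
| Random 4, 6 or 8 | 2.1% | 68.1% |

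Over 174 allocations, certain predictions fall from 58 to 174 × 0.021 ≈ 4 with sizes 4, 6 and 8. Best-guess accuracy falls by less than three percentage points.

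**The case against.** A reader might infer that concealment fails and that a third of allocations will in fact be foreseen. The article does not support that, for four reasons.

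- Foreknowledge biases selection only if it reaches someone who influences enrolment or its timing. The article does not say that the researchers who screen are the unblinded doctors or are informed by them, and a condensed article may leave such detail to the full protocol.
- The unblinded staff are said to know groups and participants. It is not said that any one person follows the full sequence in order, with block boundaries and by stratum. The 33% and 71% therefore describe an ideal observer.
- The 174 is the number outstanding when the article was written. The number outstanding when the article became available is not given, so disclosure through the article may have affected fewer.
- The research lead's share in envelope custody might be read as access to the sequence. The envelopes are sealed, and the article does not say which set drives allocation. Holding a sealed set is not shown to be access.

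It is also fair to say that scheduled patients assigned consecutively leave less room for steering, that adjustment for measured prognostic factors can reduce (not remove) such a bias, and that no bias in hours or hazard ratio has been estimated.

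These points limit the size of the claim. They do not remove it. The fixed block of four and the unblinded staff are stated design choices, and nothing in the article separates those staff from recruitment.

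**Conclusion.** The point stands as a risk to allocation concealment, not as a demonstrated failure. Up to one third of allocations, about 58 of the 174 outstanding at the time of writing, are certain in advance, and up to 71% can be guessed. Both figures assume an observer who knows the block size and tracks all earlier allocations in order and within stratum. Harm further requires that this observer can influence who is enrolled or when, or informs someone who can. The article neither states nor excludes that. How far the primary outcome could be biased cannot be sized from the document. The change is worth making because it is cheap and closes off a bias that blinded assessment cannot correct.

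**What to change.** 1. From the next unopened block, regenerate the remaining list within each surgery stratum, using randomly varying block sizes (4, 6 and 8 would serve). Do not disclose the sizes to recruiting or treating staff.
2. State that the staff who screen, obtain consent and schedule patients are separate from the TEAS doctors and anesthesiologists and are not told allocations by them. This is essential, because varying the sizes removes nearly all certain predictions but leaves a best guess right about 68% of the time.
3. Open each envelope only after consent and eligibility have been recorded.

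The cost is a new list, new envelopes and a short amendment, with no extra patients. The statistical price is a slightly larger possible imbalance between arms at the end of the trial.

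### The head of the research group is a named custodian of the allocation envelopes, which weakens allocation concealment for the assignments still to be made

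*Protocol article*

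**What the plan says.** Four statements in the protocol article bear on this, all under Randomization and blinding.

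- The list: a "computer-generated blocked randomization list with 70 blocks of four patients per block", with patients "consecutively randomly assigned to the TEAS group or the sham group at a ratio of 1:1".
- The mechanism: "Allocation shall proceed via duplicate, sealed, numbered envelopes".
- The custodians: the envelopes are "stored by the clinical trial quality control inspectors and the main person in charge of this research group".
- The rule on opening: "The blind bottom shall not be opened without reason during the trial".

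The same section says that the doctors "who will conduct the TEAS stimulation and the anesthesiologists will know the grouping information and participants". It keeps outcome assessors and statisticians apart from treatment.

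Two statements under Trial design give the setting. The first is "The trial is a single-center, prospective, randomized controlled trial (RCT) with a two-arm, parallel-group design". The second, after Fig. 1, is on recruitment: "The researchers will conduct screening in accordance with the established criteria and pre-standard treatment plan". Neither says who opens an envelope or whether the head of the group takes part in screening.

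**The concern.** Allocation concealment means that nobody who can influence which patient enters next, or when, can learn the next assignment. Envelopes can achieve this if they are kept away from the group that recruits. Here the article places them, at least in part, with the head of that group. This is a stated arrangement, not a detail left out for brevity.

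If an upcoming assignment becomes known, patients can be approached, delayed or passed over according to their expected recovery. Such selection happens before randomization. Blinded outcome assessment does not remove it, because the outcomes would be measured correctly in arms that were not comparable. Analysis by intention to treat does not remove it either, because the patients would be analysed in the arms to which they were steered. Even without any misuse, the trial would find it harder to show that concealment was intact.

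**Working it through.** The article gives no figure on this point to reproduce, so the check is mainly a reading of the stated arrangement.

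**1. What can the custody sentence mean?** It names two copies and two custodians, and allows two readings.

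- Separate copies: the inspectors hold one and the head of the group holds the other. The head then has unsupervised access to every unopened assignment.
- Joint custody: both parties hold the envelopes together. Access may then be supervised, but the head remains one of the people with access.

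Under both readings someone in the research group can reach upcoming allocations. The readings differ in how easily, not in whether.

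**2. What does each stated safeguard protect?**

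| Safeguard in the article | Deters or reveals a swapped or skipped assignment | Prevents or reveals a look at the next assignment by a custodian |
|---|---|---|
| Numbering and consecutive use | Yes | No |
| Second copy with the inspectors | Yes, on later comparison | No |
| Seal | Partly | Only if the seals are inspected |
| Bar on opening without a reason | Depends on compliance | Depends on compliance |
| Assessors and statisticians kept out of treatment | No (protects assessment) | No (protects assessment) |

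The right-hand column contains no safeguard that works independently of the custodian.

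**3. Is this the same issue as the fixed block size?** No. A block of four with two patients per arm has 6 possible orders.

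- In 2 of these orders (two alike, then the other two) the last two places are determined once earlier ones are known. In the other 4, only the last place is.
- Determined places per block: (2 × 2 + 4 × 1) / 6 = 8/6 = 1.33, that is 1.33/4 = 33% of assignments, or 1.33 × 70 = about 93 of 280.
- Best-guess success by place: 1/2, 2/3, 2/3 and 1. The mean is 2.83/4 = 70.8%.

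These rates assume one list, or one list per surgery type with the type known. Someone who sees the envelope contents knows 100%. Varying the block sizes would reduce the first problem and leave custody untouched.

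**4. How many allocations can still be protected?** The list covers 70 × 4 = 280 assignments. Trial status reports 106 participants recruited. 280 − 106 = 174. This is an upper limit, because recruitment has continued since that count.

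**5. Is there room for selection at all?** Sample size calculation gives 400–500 gastrointestinal operations a year and a period of 2 years: 2 × 400 = 800 to 2 × 500 = 1,000 operations for 280 places. An unknown share of these is eligible, so this shows only that there may be slack in whom to approach and when.

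**The case against.** The strongest case on the other side has four parts.

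**The head may not recruit.** A reader might infer that the custodian leads the people who screen and enrol, and so could steer recruitment directly. The article does not support this. It attributes screening to the researchers in general and names no enroller. This objection stands: no route from custody to recruitment is documented. The custody weakness remains, because concealment should not depend on the discretion of anyone inside the group that runs the trial.

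**A separate full set is not stated.** A reader might also infer that the head holds a complete copy alone. That is a natural reading of two copies and two custodians, but joint custody also fits the words. The point therefore has to rest on access, which both readings give.

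**There are safeguards.** The list is computer-generated, the envelopes are sealed and numbered, a second party is named, and opening is restricted. These deserve credit, and the second copy is a real check against altered assignments. It does not guard against a look at the next one. The permitted reasons for opening, an opening log and the route for emergency disclosure are operational details that an article may leave to the full protocol. Their absence is not held against the plan here.

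**The harm cannot be sized.** One could suppose that 10% of patients were steered on a prognostic difference of 12 to 24 h, which gives 0.10 × 12 = 1.2 h to 0.10 × 24 = 2.4 h against the 12 h effect in Sample size calculation. Neither the 10% nor the direction comes from the article, and the 12 to 24 h range is not given as a prognostic difference. The calculation is therefore not evidence and is not relied on.

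That the treating doctors and anaesthesiologists know the assignments is a matter after allocation. It does not make a sealed future envelope easier to read.

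**Conclusion.** The point holds as a weakness in how concealment is arranged. The article makes the head of the research group a custodian of the allocation envelopes in a single-centre trial, and nothing it states would prevent or reveal a custodian's look at the next assignment. This follows from the custody sentence under either reading of it.

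It is not evidence of a breach, and it does not show that the results are biased. The size of any bias cannot be estimated from the document. The only defensible count is the allocations still open to protection: at most 174 of 280. The conclusion assumes that the article describes custody as practised, and that the head belongs to the group responsible for recruitment in a broad sense, without assuming that the head enrols patients. It ranks as a worthwhile, inexpensive improvement.

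**What to change.** For the allocations still to be made:

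1. Take all unopened envelopes out of the research group's custody, and check and record at the handover that they are intact.
2. Keep them with the quality control inspectors already named, after confirming that the inspectors are independent of recruitment. The article does not say so.
3. Have the inspectors release the next numbered envelope only after consent and eligibility are recorded.

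Replacement text could read: *Both copies of the allocation envelopes are held by the quality control inspectors, who take no part in recruitment. They release the next envelope in numerical order once consent and eligibility have been recorded. No member of the research group holds unopened envelopes.*

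**Cost.** This is a minor amendment or a note to file. It leaves eligibility, treatment, endpoints and sample size unchanged. The inspectors take on a small release step before each operation, early enough for stimulation to begin before induction as the article plans. The group lead must ask them for any disclosure. Placing both copies with one party gives up the cross-check between two holders, but recorded assignments can still be compared with the computer-generated list. The change does nothing for assignments already made. For those, the report can only describe the custody that applied.
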